### Study hypotheses

We assume that the number of pharmaceutical agents taken by the patient can be reduced in the intervention group. We will compare the change in medication intake between baseline and follow-up in the intervention and control group. We expect that the mean difference between the changes in both groups will be at least 1.5 drugs less in the intervention group. A minimum difference of 0.5 drugs between both groups is defined as clinically relevant.

It is assumed that a reduction of medications used will not impair quality of life. We will compare the change in health related quality of life between baseline and follow-up in the intervention and control group. We expect that the mean change in the intervention group will not be statistically significantly inferior to the mean change in the control group.

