### Sample size/power calculations

For the sample size estimation of both endpoints an α=0.025 is assumed in order to adjust for multiple testing. The sample size calculation is based on preliminary analyses of the baseline assessment of the MultiCare Cohort study, which used the same inclusion criteria that are scheduled for this trial and also recruited patients via GP surgeries. In the MultiCare Cohort study patients averagely used 7.26 ± 3.5 medications (Median 7). We expect a mean reduction of 1.5 drugs per patient in the intervention group (difference baseline – follow-up) and no change (mean reduction 0) in the number of drugs in the control group (effect-size: 0.429). A common standard deviation of 3.5 drugs is assumed. Based on the data of the MultiCare Cohort study the intracluster correlation is ρ=0.14 and a minimum of 10 patients per GP are targeted. Under these assumptions and with α=0.025 and a power of 80% totally 48 GPs (475 patients) are necessary to detect the expected difference (2-sided t-test for equal variances). Given a drop-out rate of 20%, 594 patients (and 60 GP surgeries) are needed altogether. The dropout rates in other multicenter studies of the principal investigators are comparable (e.g. AgeCoDe: 16% within 1.5 years).

Regarding the other primary endpoint it is assumed that health related quality of life will not be inferior in the intervention group compared with the control group at the end of the intervention. On the instrument used (EQ-5D value set UK [20]) -0.59 till 1.0 points can be achieved. At the baseline assessment of the MultiCare Cohort study patients scored 0.68 ± 0.30 points. For testing non-inferiority it is assumed that the mean score of the intervention group at the end of the intervention is at most half a standard deviation (i.e. 0.15 points) less than that of the control group. Given a standard deviation of 0.30, an α=0.025, a power of 80%, an intra-cluster correlation of ρ=0.14, 128 patients are needed (1-sided test). Considering a design effect of 2.26 (minimum of 10 patients per GP) and a dropout rate of 20% we would need 362 patients altogether. As this number of patients is smaller than that for the other primary endpoint, the inclusion of 600 patients will be sufficient also for this health related quality of life endpoint. Statistical analyses will be on the intention to treat basis.

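### The quality-of-life hypothesis asks only for no statistically significant inferiority, with no margin, and does not match the 0.15-point non-inferiority test used for sample size

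*Protocol article*

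**What the plan says.** The protocol article describes the quality-of-life endpoint in three places.

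- **Study hypotheses.** "We expect that the mean change in the intervention group will not be statistically significantly inferior to the mean change in the control group". The quantity is change from baseline to follow-up. No margin appears.
- **Sample size/power calculations.** The planned non-inferiority test works from this premise, with control as the comparator: "the mean score of the intervention group at the end of the intervention is at most half a standard deviation (i.e. 0.15 points) less". The quantity is the score at the end of the intervention. The inputs are SD 0.30, one-sided α of 0.025, 80% power and an intracluster correlation of 0.14, giving 128 patients before clustering. Then: "Considering a design effect of 2.26 (minimum of 10 patients per GP) and a dropout rate of 20% we would need 362 patients altogether". The α is explained by the two primary endpoints: "For the sample size estimation of both endpoints an α=0.025 is assumed in order to adjust for multiple testing".
- **Statistical analyses.** Multi-level models with a GP random effect, adjustment for baseline imbalance, intention to treat and Bonferroni correction are named. No margin or confidence-limit rule is given for quality of life.

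**The concern.** An intervention arm that is not significantly worse has only failed to reject equality. That does not show that a loss of a given size has been excluded. Such a rule becomes easier to meet as the estimate becomes less precise, for example with more drop-out or stronger clustering. A margin test works the other way: imprecision makes it harder to pass, and its false-success rate at the margin stays at the nominal level.

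The article thus gives two non-equivalent statements of what is to be shown for a primary endpoint, and on some data they disagree. The quantity also differs (change against end score), and so may the time point: the Intervention section gives 12 months of intervention but follow-up at 14 months. Half of the headline claim, fewer drugs without loss of quality of life, depends on this endpoint.

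**Working it through.** **Reproducing the plan's figures.** Inputs from Sample size/power calculations: margin 0.15, SD 0.30, one-sided α 0.025, power 80%, intracluster correlation 0.14, 10 patients per GP, drop-out 20%. Two assumptions are not stated but are consistent with the result: true difference 0 and 1:1 allocation.

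- Normal formula: 2 × (1.960 + 0.842)² × (0.30/0.15)² = 62.8, so 63 per arm and 126 in total. The noncentral t version gives 64 per arm, **128** in total, with power 80.1%.
- Design effect: 1 + (10 − 1) × 0.14 = 2.26. Then 128 × 2.26 = 289.3, and 289.3/0.80 = 361.6, so **362**.

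Both figures reproduce under the margin test.

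**Comparing the two rules.** Let N_eff be the number evaluable divided by the design effect, and SE = 0.30 × √(4/N_eff). Both rules are taken at one-sided 0.025, with a normal approximation.

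- Hypothesis wording is met if the observed loss is below 1.96 × SE. For a true loss L, the probability is Φ(1.96 − L/SE).
- Margin test is passed if the observed loss is below 0.15 − 1.96 × SE. For a true loss L, the probability is Φ((0.15 − L)/SE − 1.96), which is 2.5% at L = 0.15 whatever the SE.

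For 480 completers (600 less 20%), two design effects are shown: 2.26 as stated, and 1 + (8 − 1) × 0.14 = 1.98, because 480 patients over the planned 60 surgeries is 8 per GP.

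| Case | N_eff | SE | Wording met if loss below | Margin test passed if loss below | Wording met at true loss 0.15 |
|---|---|---|---|---|---|
| Endpoint's own requirement | 128 | 0.0530 | 0.104 | 0.046 | 19% |
| 480 completers, design effect 2.26 | 212.4 | 0.0412 | 0.081 | 0.069 | 4.6% |
| 480 completers, design effect 1.98 | 242.4 | 0.0385 | 0.076 | 0.074 | 2.7% |
| All 600 evaluable, design effect 2.26 | 265.5 | 0.0368 | 0.072 | 0.078 | 1.7% |

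In the second row, an observed loss between 0.069 and 0.081 passes the hypothesis wording and fails the margin test. In the last row the conflict reverses: a loss between 0.072 and 0.078 fails the wording and passes the margin test.

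The thresholds coincide only when 1.96 × SE = 0.15 − 1.96 × SE, that is at SE = 0.15/3.92 = 0.0383. The planned trial happens to lie near that value, which is why the gap there is small. To show the dependence on precision, at a hypothetical N_eff of 20 (SE 0.134) the wording would be met 80% of the time at a true loss of 0.15.

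**Effect of the fix.** With the 475 evaluable patients required for the medication endpoint, SE = 0.30 × √(4/210.2) = 0.0414. Power of the margin test at no true difference is Φ(0.15/0.0414 − 1.96), about 95%.

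**The case against.** The sentence begins as an expectation and stands under Study hypotheses. The parallel sentence on medication, expecting a difference of at least 1.5 drugs, is plainly not a success criterion. The sample size section already gives a margin, a side and an α, so a margin test was evidently intended. A condensed article may leave the exact confidence-limit wording to a fuller document. All of this stands, and it limits the point to a conflict between two statements. It does not remove the conflict: the sentence is the only wording of the quality-of-life hypothesis in that section, it names a different rule, and nothing says which one governs.

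It can also be said that, under randomisation, the difference in mean change and the difference in mean end score have the same expectation. That is correct, so the margin can be carried from one scale to the other. The standard deviations need not agree, however: with equal variances and baseline correlation r, the SD of change is 0.30 × √(2(1 − r)), which equals 0.30 only at r = 0.5. The article gives no r.

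A reader might infer stronger points that the document does not support:

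- **That success will be declared on a non-significant result.** No section says so.
- **That passing at a true loss of 0.075 or 0.10 is a false success.** Both lie inside the 0.15 margin and count as non-inferior by the plan's own definition.
- **That the error rate is badly inflated at the planned size.** It is 2.7 to 4.6% with 480 completers, and below 2.5% if all 600 are evaluable.
- **That larger inflation follows from a two-sided Bonferroni test at 0.025.** The sample size section specifies a one-sided test at 0.025 for this endpoint.

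**Conclusion.** The point holds as an inconsistency in a primary hypothesis. The hypothesis wording has no margin and, used as a criterion, would take absence of significance for non-inferiority. The sample size section describes a proper margin test on a differently defined quantity, and the analysis section does not reconcile them.

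The practical size is modest at planned retention: at a true loss equal to the margin, the wording is met about 3 to 5% of the time against 2.5%, and the band of observed losses with opposite verdicts is at most about 0.012 wide (0.081 − 0.069). At the endpoint's own minimum sample it is large (19% against 2.5%), and at full retention it reverses (1.7%). The defect is that the error rate depends on retention and precision instead of being fixed in advance.

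These figures rest on SD 0.30 for whichever quantity is analysed, the stated intracluster correlation, 1:1 allocation and a normal approximation without any precision gain from baseline adjustment. Such a gain would move the comparison towards the reversed case. The sample size arithmetic is not in question.

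**What to change.** Replace the sentence under Study hypotheses with a rule of this kind: non-inferiority in EQ-5D is concluded if the lower one-sided 97.5% confidence limit for the difference (intervention minus control, adjusted for baseline, at follow-up, from the model with a GP random effect) lies above −0.15. Use the same quantity and time point in Sample size/power calculations, and refer to the rule under Statistical analyses.

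The cost is wording only. The 128 and 362 patients stay as they are, and no extra recruitment or data collection is needed. The change should be dated before any comparison of outcomes by group.

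### The quality-of-life hypothesis is worded as absence of significant inferiority, with no margin, while the sample size section plans a one-sided test against a 0.15-point margin, and on a different quantity

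*Protocol article*

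**What the plan says.** The article describes the quality-of-life endpoint in three places.

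- **Study hypotheses.** The expectation is that "the mean change in the intervention group will not be statistically significantly inferior to the mean change in the control group". No margin is given, and the quantity is change from baseline to follow-up.
- **Sample size/power calculations.** Non-inferiority is framed by a margin: "the mean score of the intervention group at the end of the intervention is at most half a standard deviation (i.e. 0.15 points) less" than in the control group. The inputs are "Given a standard deviation of 0.30, an α=0.025, a power of 80" percent and "an intra-cluster correlation of ρ=0.14". The result is "128 patients are needed (1-sided test"), then "Considering a design effect of 2.26 (minimum of 10 patients per GP") and "a dropout rate of 20% we would need 362 patients altogether". The quantity is the end score.
- **Statistical analyses.** This section names multilevel models with GP as random effect, adjustment for baseline imbalances, intention to treat and Bonferroni correction. It mentions neither a margin nor a choice between change and end score.

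**The concern.** The two statements have different null hypotheses. In the hypotheses section the implied null is no difference, and success is failing to reject it. In the sample size section the null is a loss of 0.15 or more, and success is rejecting it. Failing to find a significant loss is not evidence that a relevant loss is absent. It can equally reflect too few patients, drop-out or noisy measurement.

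The claim that medication can be reduced without impairing quality of life is half of the trial's primary hypothesis. If the hypothesis sentence were used to judge it, lower precision would make the claim easier to reach, and the 2.5% error rate behind the sample size would no longer be guaranteed. The differing quantities (change or end score) leave a second choice open for the same primary endpoint.

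**Working it through.** **Inputs from the sample size section.** Margin 0.15; SD 0.30; one-sided α = 0.025 (z = 1.96); power 80% (z = 0.842); intracluster correlation 0.14; 10 patients per GP; drop-out 20%; planned inclusion 600 patients, about 60 GPs. Equal allocation and a true difference of zero are my assumptions for the sizing check.

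**Step 1: reproduce the plan's figure.** The normal approximation gives n per arm = 2 × (1.96 + 0.842)² × 0.30² / 0.15² = 62.8, so 63. The t-based version gives 64 per arm, or 128 in total, as stated. Design effect = 1 + (10 - 1) × 0.14 = 2.26. Then 128 × 2.26 = 289 evaluable, and 128 × 2.26 / 0.8 = 361.6, so 362, as stated. The trial was therefore sized for a margin-based test.

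**Step 2: put both readings on one scale.** For N evaluable patients and design effect D, SE = 0.30 × √(4D/N).

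- Non-significance reading: passes if the estimate (intervention minus control) exceeds -1.96 × SE.
- Margin rule: passes if the estimate exceeds -0.15 + 1.96 × SE.

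Pass probabilities come from a normal distribution centred at minus the true loss. Both readings use one-sided 0.025.

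| Scenario | SE | Cut-off, non-significance | Cut-off, margin | Pass at true loss 0.10 | Pass at true loss 0.15 |
|---|---|---|---|---|---|
| 60 GPs × 8 completers = 480, D = 1 + 7 × 0.14 = 1.98 | 0.0385 | -0.076 | -0.074 | 26.3% vs 25.4% | 2.7% vs 2.5% |
| 480 evaluable, D = 2.26 | 0.0412 | -0.081 | -0.069 | 32.0% vs 22.8% | 4.6% vs 2.5% |
| 289 evaluable, D = 2.26 | 0.0531 | -0.104 | -0.046 | 53.0% vs 15.4% | 19.3% vs 2.5% |
| 600 evaluable (no drop-out), D = 2.26 | 0.0368 | -0.072 | -0.078 | 22.5% vs 27.4% | 1.7% vs 2.5% |

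The last two columns give the non-significance reading first and the margin rule second.

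**Step 3: where the order reverses.** The cut-offs meet when 1.96 × SE = 0.075, i.e. SE = 0.0383. At SD 0.30 and D = 2.26 that is N = 4 × 2.26 × 0.30² / 0.0383² ≈ 556. At 480 evaluable and D = 2.26 it is an effective SD of about 0.279. The article gives no SD of change, so the SD is open. If, as an assumption, baseline and follow-up correlate at 0.7, the SD of change is 0.30 × √(2 × 0.3) = 0.232. At 480 evaluable and D = 2.26 a true loss of 0.15 then passes 0.3% of the time, against 2.5% under the margin rule.

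**The case against.** The strongest reply is that the hypotheses section states an expectation, not a decision rule. The paragraph before it, on the drug count, is phrased the same way, and nobody would take its expected 1.5-drug difference as a success threshold. The sample size section already names the test, the margin, the level and the sidedness. An exact confidence-limit rule commonly belongs in the analysis plan, which is not shown, so its absence from the statistical analyses section is not itself a fault.

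Most of this stands. It is not established that the trial would be judged by non-significance, and the criticism does not rest on missing detail. What remains is that the article makes two statements about one primary endpoint that disagree on the null hypothesis and on the quantity compared, and nothing in it gives one precedence.

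A reader might also infer that the hypotheses wording lets real losses through more often as a rule. The documents do not support that. If drop-out is spread over 60 practices the two readings nearly coincide, and with less drop-out or a smaller effective SD the non-significance reading becomes the stricter one. It would then fail trials that meet the margin. The 19% figure needs 289 evaluable patients. The 362 recruits behind it are a check that this endpoint does not drive the sample size, not a planned size.

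**Conclusion.** The contradiction is real. The hypothesis is framed as absence of significant inferiority in change scores, while the sizing is for exclusion of a 0.15-point loss in end scores. Taken as a criterion, the hypothesis wording does not control the error at the 0.15 margin and grows more lenient as precision falls.

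On the plan's own inputs the effect at the planned size is small: 2.7% to 4.6% acceptance of a true 0.15 loss, against 2.5%. It becomes material only with a marked loss of precision. These figures assume SD 0.30 for the analysed quantity, equal allocation, one-sided 0.025 for both readings and a normal approximation. The direction is not fixed, because the SD of change and the gain from adjustment are not given.

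**What to change.** Replace the sentence in Study hypotheses with: *Non-inferiority is concluded if the lower limit of the confidence interval (one-sided α = 0.025) for the intervention-minus-control difference in EQ-5D, from the multilevel model with GP as random effect, lies above -0.15.*

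Name one quantity, either change from baseline or baseline-adjusted end score. Use the same rule and quantity in Study hypotheses, Sample size/power calculations and Statistical analyses.

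The cost is a few lines of wording, settled before outcome data are seen. No extra patients are needed: the planned 594 to 600 already exceed the 362 computed for the margin test.

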### Secondary outcome measures

We will assess the following secondary outcome measures:

a. GP’s knowledge about the medication taken by the patient (including GP’s own prescriptions, prescriptions of other specialists, and use of over the counter drugs). We will assess the medication documented in GP charts at baseline and follow up and compare it with the medication data collected in patient interviews using similarity measures as the Jaccard coefficient [16]. We expect that the GP’s knowledge will increase due to our intervention.

b. Patient satisfaction with GP services as measured by the EUROPEP [17] and patient empowerment as measured by the Health Care Empowerment Questionnaire [18], both collected in patient interviews. We assume that patient satisfaction and empowerment will improve.

c. Health care utilization and costs, assessed in a comprehensive way by the Leipzig Supply and Cost Instrument [19] in patient interviews as well as number of contacts with the GP and GP’s referrals to specialists assessed in GP interviews.

### Methods against bias

Selection bias will be minimised by a standardised recruitment procedure (chart registry), performed by trained research assistants. In order to collect the required data for a CONSORT flow chart (for clustered trials), the full recruitment process will be documented.

#### **Public registration**

Before start, the study was registered in a public internet trial archive (ISRCTN46272088).

#### Blinding

Participants (GPs and patients) will not be blinded to their assignment (which is practically not possible) but will be unaware of the study hypotheses or primary outcome measures.

#### Standardization of assessments

To ensure high data quality assessors will be trained on standardised patients. The personnel of the participating practices will not be involved in the collection of data.

#### Monitoring

An independent monitor (Institute for Biometry, Hannover Medical School) will conduct data monitoring to ensure high quality data in adherence to the study protocol.

#### Detection bias

The statistical analysis of endpoints will be performed by a statistician blinded to group assignment.

GPs of the control group will be offered the two training sessions at the end of the intervention in order to avoid a possible lack of motivation for recruitment and documentation. Furthermore they will get the same financial incentive as the GPs of the intervention group.

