### Intervention

GPs allocated to the intervention arm will receive an educational intervention: (1) on performing a narrative doctor-patient-dialogue reflecting treatment targets and priorities of the patient, and (2) on performing a narrative patient-centred medication review.

During the one year intervention GPs will have a total of three conversations with the enrolled patients instead of routine consultations. Each conversation is scheduled for about 30 minutes. The first conversation will focus on treatment targets and priorities of the patient, the second will focus on the medication taken by the patient and the third will combine the elements of both previous conversations.

The idea behind the approach of installing a structured framework of regular consultations is that this will eventually reduce the high number of (often unscheduled) consultations. The concept of narrative medicine shall facilitate the development of the patient’s own agenda.

Follow-up per patient: 14 months after the baseline interview; duration of intervention per patient: 12 months; all additional treatments are allowed.

GPs of the control group will perform care as usual and at the end of the intervention they will be offered to participate in a similar educational intervention as in the intervention group given. This offer will outweigh the possible lower level of motivation of these GPs of having been randomised to the control arm. GPs of the control group will also be financially recompensated equally to the GPs of the intervention group.

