### Randomization

The randomization will be carried out as a cluster randomization, in which the GPs will be allocated either to the intervention or to the control group. Randomization will be performed successively when patient recruitment in the respective surgery is finished. It will be performed by an experienced independent institute (Institute for Biometry, Hannover Medical School).

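### The training offer to control GPs is tied to the end of the intervention rather than to completed follow-up, so the wording allows control GPs to be trained before outcomes are measured

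*Protocol article*

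**What the plan says.** Two sections of the protocol article give the timing of the offer to control GPs. Under Intervention: "at the end of the intervention they will be offered to participate in a similar educational intervention as in the intervention group given". Under Detection bias: "GPs of the control group will be offered the two training sessions at the end of the intervention". Neither mentions the follow-up interview, and no other section holds the offer back until outcomes have been collected.

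The Intervention section also sets the two durations: "Follow-up per patient: 14 months after the baseline interview; duration of intervention per patient: 12 months". The 14 months run from the baseline interview. The starting point of the 12 months is not given.

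Three further statements bear on the timing:

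- Randomization: "Randomization will be performed successively when patient recruitment in the respective surgery is finished".
- Study hypotheses: "We will compare the change in medication intake between baseline and follow-up in the intervention and control group".
- Sample size/power calculations, on the EQ-5D: "health related quality of life will not be inferior in the intervention group compared with the control group at the end of the intervention".

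**The concern.** The offered training is described as similar to that of the intervention arm, which includes a patient-centred medication review. That component acts directly on the first primary outcome, the number of drugs taken. The offer is anchored to an event that may come before the 14-month assessment. If so, some control GPs could apply the training while their patients are still waiting to be assessed.

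Three comparisons would be touched:

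- **Medication.** The sample size assumes no change in the control arm. Any reduction there shrinks the difference.
- **GP knowledge of medication.** This is derived from GP charts at baseline and follow-up. A newly trained control GP could update charts quickly, so this outcome may react even to a short window.
- **Quality of life.** Contamination pulls the arms together. In a non-inferiority comparison this hides part of a real loss, if there is one.

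**Working it through.** **1. The possible window.** Let *s* be the months from a patient's baseline interview to the start of that patient's 12 months. Follow-up is at month 14 and the intervention ends at month *s* + 12, so the window is 14 − (*s* + 12) = 2 − *s* months, and not below 0.

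- *s* = 0 (the 12 months start at the baseline interview): 2 months.
- *s* of 2 or more (for example, time taken by recruitment, randomization and GP training): 0 months.

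The article does not give *s*. Nor does it say whether the end of the intervention is meant per patient, per surgery or for the whole trial. Training is given to a GP, but follow-up is counted per patient. Suppose a surgery's training date were set by its first patient, with *s* = 0. A patient interviewed *d* months after that first patient would then have a window of 2 + *d* months. If the offer came at the end of the whole trial, there would be no window.

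**2. The plan's own sample size.** Inputs from Sample size/power calculations: difference 1.5 drugs, SD 3.5, two-sided α = 0.025, power 80%, intracluster correlation 0.14, 10 patients per GP, dropout 20%.

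- Two-sample t-test: 104.77, rounded up to 105 per arm, 210 in total.
- Design effect: 1 + (10 − 1) × 0.14 = 2.26.
- 210 × 2.26 = 474.6, i.e. 475. The stated figure is reproduced.
- 475 / 0.8 = 593.75, i.e. 594. The stated figure is reproduced.

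**3. Power under dilution.** Effective patients per arm: 475 / 2.26 / 2 = 105.1. Standard error of the difference: 3.5 × √(2 / 105.1) = 0.483. Power = Φ(difference / 0.483 − 2.241).

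Dilution is the share of the full effect that the control arm as a whole has realised by follow-up, that is, the share of controls exposed times the share of the effect reached. The document gives neither share, so these are assumptions.

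| Dilution | Example | Difference (drugs) | Power |
|---|---|---|---|
| 0% | no control patient exposed | 1.500 | 0.81 |
| 5% | 10% exposed, half the effect | 1.425 | 0.76 |
| 10% | 10% exposed, full effect; or 20% exposed, half the effect | 1.350 | 0.71 |
| 20% | 20% exposed, full effect | 1.200 | 0.60 |

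**4. Quality of life.** The stated margin is 0.15 points. If the intervention truly cost 0.15 points, and if dilution of the same size applied, the difference seen would be 0.15 × 0.9 = 0.135 at 10% and 0.15 × 0.8 = 0.12 at 20%. Both lie inside the margin. If there is no true loss, dilution has nothing to mask.

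**The case against.** The best defence is that the two end points may coincide. The 14 months start at the baseline interview. A surgery is randomized only after its recruitment is finished, and intervention GPs must be trained before the first conversation. The extra two months could simply be lead-in. The sample size section supports this reading, because it places the EQ-5D comparison at the end of the intervention as if that were the follow-up assessment. This stands: an overlap is not demonstrated.

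A second argument is that a condensed article may leave the exact date of a deferred training offer to the full protocol. This carries less weight, because the article does state a timing rule, twice, and ties it to an event other than outcome assessment.

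A third argument concerns size, and it stands. Training is only offered; a GP must accept it, attend two sessions and then put it into practice. In the intervention sequence, medication is the focus only of the second conversation. The medication survey covers products used in the previous twelve months, so a drug stopped shortly before follow-up may still be recorded. Dilution of 10% to 20% across the whole control arm would need fast and wide uptake.

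A reader might go further and infer that the control arm will be contaminated for two months, or that the quality-of-life result is biased towards non-inferiority in any case. The article supports neither. The first needs *s* = 0 plus actual uptake. The second holds only if the intervention truly lowers quality of life; if it raises it, dilution works against the non-inferiority claim.

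**Conclusion.** The point holds as an unprotected timing rule. Read literally, the article permits control GPs to be trained 0 to 2 months before a patient's follow-up, and possibly earlier relative to patients interviewed late in a surgery. Nothing in it rules this out. It does not show that this will happen.

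The power figures of about 81%, 71% and 60% illustrate 0%, 10% and 20% dilution. They rest on the plan's own SD, intracluster correlation and 475 evaluable patients; the dilution itself is assumed. The short window, voluntary uptake and twelve-month recall make the low end of dilution, including none, the more likely case. Planned power is only about 80%, so there is little reserve. The change is worth making because it removes an avoidable risk at almost no cost, not because a large loss is expected.

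**What to change.** In both the Intervention and the Detection bias sections, state that training is offered to a control GP only after the last 14-month patient interview, the GP interview and the chart extraction in that surgery are complete. In Sample size/power calculations, reconcile the EQ-5D time point with the 14-month follow-up. Stating when the 12 months begin relative to the baseline interview would settle the remaining ambiguity.

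The cost is a few sentences and a slightly longer wait for control GPs. The article gives the offer partly to sustain motivation for documentation, and holding it until documentation is complete serves that purpose as well. Sample size and analysis are unchanged.
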